#### 11.4.1.2 Visit 1 ( start of intervention , Week 1)

If all tests and eligibility assessments are completed during the screening visit, Visit 1 can be conducted on the same day to assign participant numbers. If the screening visit and assignment of participant numbers occur on the same day, overlapping evaluations are performed only once.

- ① Measure vital signs.
- ② Investigate past and current medical history (changes between Visit 0 and Visit 1).
- ③ Assign random numbers.
- ④ Prescribe a four-week supply of the assigned herbal medicine based on the random number.
- ⑤ Participants follow the investigator's instructions for the following evaluations:
  - Assess fatigue severity using a 0-100 VAS.
  - Evaluate fatigue using the Chalder Fatigue Scale (ChFS).
  - Assess quality of life using EQ-5D-5L.
  - Evaluate sleep status using PSQI-K (Korean version of the Pittsburgh Sleep Quality Index).
  - Conduct cognitive function tests using K-MOCA (Korean-Montreal Cognitive Assessment).
  - Evaluate depression using Beck's Depression Inventory (BDI).

- Perform digit span tests (forward and backward).
- Conduct computerized neurocognitive function tests.
- Perform the Short Physical Performance Battery (SPPB).

#### **11.4.1.3 Visits 2 and 3 (mid-term visit, Week 4 ( 28 days) $\pm 2$ days, Week 8 ( 56 days) $\pm 2$ days)**

The following tests are conducted during mid-term visits:

- ① Measure vital signs.
- ② After collecting the prescribed herbal medicine from the previous visit, verify the dosage taken.
- ③ Participants follow the investigator's instructions for the following evaluations:
  - Fatigue assessment using FSS.
  - Evaluate fatigue using the Chalder Fatigue Scale (ChFS).
  - Assess fatigue severity using a 0-100 VAS.
- ④ Prescribe a four-week supply of the clinical trial medication based on the random number.
- ⑤ Investigate concomitant medications.
- ⑥ Confirm any adverse reactions after taking the clinical trial medication.

#### **11.4.1.4 Visit 4 (End of Intervention, Week 12 (84 days) $\pm 2$ days)**

During Visit 4, the administration of the clinical trial medication is completed, and the following tests are conducted, marking the end of the clinical trial.

- ① After collecting the prescribed herbal medicine from the previous visit, verify the dosage taken.
- ② Measure vital signs.
- ③ Conduct blood tests and ECG:
  - Blood chemistry : AST , ALT , BUN, creatinine
  - Electrocardiography: EKG
- ④ Collect blood samples for immune and metabolite tests:
  - Immunology: COVID-19 specific antibody/neutralizing antibody tests, single-cell transcriptome analysis (scRNA seq.) for immune-related gene expression comparison, FACS for immunophenotyping, serum cytokine levels.
  - Metabolomics: primary and secondary metabolite profiling.
- ⑥ Participants follow the investigator's instructions for the following evaluations:

- Fatigue assessment using FSS.
  - Evaluate fatigue using the Chalder Fatigue Scale (ChFS).
  - Assess fatigue severity using a 0-100 VAS.
  - Assess quality of life using EQ-5D-5L.
  - Evaluate sleep status using PSQI-K (Korean version of the Pittsburgh Sleep Quality Index).
  - Conduct cognitive function tests using K-MOCA (Korean-Montreal Cognitive Assessment).
  - Evaluate depression using Beck's Depression Inventory (BDI).
  - Perform digit span tests (forward and backward).
  - Conduct computerized neurocognitive function tests.
  - Perform the Short Physical Performance Battery (SPPB).
- ⑤ Investigate concomitant medications.
- ⑥ Confirm any new adverse reactions since the last visit and follow up on previously reported adverse reactions.
- ⑦ Conclude the study and provide guidance for any necessary follow-up visits.

#### **11.4.1.7 Unscheduled Visit**

If a participant visits on a non-scheduled date due to adverse reactions, changes in concomitant medications, early dropout, or the need for medical treatment based on clinical trial measurements, document the related details as thoroughly as possible. Ensure that the planned trial schedule is not altered due to unscheduled visits. Visits to the hospital due to underlying conditions or screenings not related to the primary condition planned for the clinical trial are not considered unscheduled visits.

Unscheduled visits can occur as needed based on participant requests or investigator judgment. During these visits, conduct all tests corresponding to Visit 4 as much as possible, but do not impose strict restrictions, allowing for additional appropriate tests based on the investigator's discretion.

#### **11.4.2 Observation items**

##### **11.4.2.1 Participation in other clinical trials**

To prevent participants from concurrently participating in other clinical trials, establish an identity verification process and confirm their participation in other clinical trials during each visit, including the screening visit. Participants cannot enroll in this study if they have participated in another study within the last 30 days.

**11.4.2.2 Demographic survey**

Collect information on date of birth, age, gender, height, weight, BMI, highest education level, and occupation. Record the date of birth according to the official solar calendar date on the participant's identification card, and calculate age based on the date of written consent. Participants select their highest education level from the options: below elementary school, elementary school, middle school, high school, or university and above. Occupation is categorized as physical labor, non-physical labor, or other (unemployed, etc.).

**11.4.2.3 Investigation of past and present medical history**

Investigate and record any clinically significant medical or abnormal conditions that the study subjects have experienced in the past or are currently experiencing. This includes the diagnosis, start date, end date, whether the condition persists at the time of screening, and observations. Additionally, collect information on the date of COVID-19 diagnosis. Special attention is given to conditions that might affect drug intake or absorption, such as swallowing disorders, severe digestive disorders, galactose intolerance, Lapp lactase deficiency, glucose-galactose malabsorption, and other genetic problems. Also investigated are past histories of heart diseases like myocardial infarction or heart failure, allergies to the study drug, liver or kidney diseases, and diabetes.

**11.4.2.4 Investigation of fatigue-related medical history**

Investigate whether the study subjects have previously experienced or are currently experiencing clinically significant conditions that could cause fatigue, such as cancer, sleep disorders, chronic hepatitis, liver cirrhosis, chronic renal failure, tuberculosis, asthma, or multiple sclerosis.

**11.4.2.5 Assessment of current fatigue symptoms**

Evaluate whether the study subjects have the following fatigue symptoms, and confirm the presence of fatigue if all criteria are met:[21, 22]

- Persistent fatigue exacerbated by physical or mental activity.
- Difficulties in at least three of the four areas: daily activities, occupational activities, social activities, and leisure activities.
- No diagnosis of physical or mental diseases causing fatigue.
- Non-refreshing sleep.

#### 11.4.2.6 Investigation of COVID-19 diagnosis

To determine the COVID-19 diagnosis, verify the following provided by the subjects: text messages from the Disease Control and Prevention Agency, COVID-19 related diagnosis or opinion documents, hospitalization records, and PCR test records at the time of diagnosis. Collect information on the vaccination status (whether vaccinated, type of vaccine, vaccination dates, and any adverse reactions) and the timing of the COVID-19 diagnosis along with the following data:

- Medical history during COVID-19 diagnosis and treatment.
- Early Warning Score (EWS).

The EWS is extracted from the subject's medical records if available, or collected based on the subject's memory if not. Evaluate EWS using SpO2, supplemental oxygen, heart rate, systolic BP, respiratory rate, body temperature, and CNS level. Classify COVID-19 severity based on the National Early Warning Score (NEWS; mild < 5, severe ≥ 5).

- 1) EWS assessment date (on the worst symptom day), respiratory rate, oxygen saturation, oxygen supplement, body temperature, systolic blood pressure, heart rate, and consciousness.
- 2) Calculate and record EWS in the Case Report Form (CRF) according to the provided table.

| 변수     | 3      | 2      | 1         | 0         | 1         | 2       | 3     |
|--------|--------|--------|-----------|-----------|-----------|---------|-------|
| 산소포화도  | 91이하   | 92-93  | 94-95     | 96이상      |           |         |       |
| 산소투여여부 | 예      | 예      | 아니오       | 아니오       |           |         |       |
| 맥박     | 40이하   |        | 41-50     | 51-90     | 91-110    | 111-130 | 130이상 |
| 수축기혈압  | 90이하   | 91-100 | 101-110   | 111-219   |           |         | 220이상 |
| 호흡수    | 8이하    |        | 9-11      | 12-20     |           | 21-24   | 25이상  |
| 체온     | 35.0이하 |        | 35.1-36.0 | 36.1-38.0 | 38.1-39.0 | 39.1이상  |       |
| 의식수준   |        |        |           | 정상        |           |         | 이상    |

#### 11.4. 2.7 Investigation of current medications

Investigate the current medications the subjects are taking. Record the drug name, usage, dosage, unit, administration route, start date, end date, and whether the medication is ongoing, as well as the purpose of the medication.

#### 11.4.2.8 Measurement of vital signs

Measure blood pressure (systolic and diastolic), body temperature, respiratory rate, and pulse rate. All measurements should be taken with the subject in a seated position after 5 minutes of rest.

#### **11.4.2.9 Electrocardiogram examination**

Evaluate for severe heart diseases such as acute myocardial infarction and ventricular fibrillation.

#### **11.4.2.10 Laboratory tests**

Conduct laboratory tests to perform a basic examination for other diseases. Specific details can be found under "Other Observation Items" in the "Observation Items and Observation Methods" section.

#### **11.4.2.11 Immunological test and metabolite analysis**

##### **1. Sample collection and storage**

##### **1.1 Blood sampling**

Blood sampling is conducted at the designated clinical trial sample analysis institution within Kyung Hee Medical Center, with consent from the subjects. Collect 25ml per draw (4 x 5ml EDTA tubes, 1 x 5ml general tube). After anonymizing samples, quickly transport them in an ice-filled cold box to ROKIT Genomics for scRNA-seq analysis. Two 5ml EDTA tubes are processed to isolate peripheral mononuclear cells using the RBC lysis method, and the remaining two using centrifugation. Blood in the 5ml general tube is separated into serum. Processed samples are temporarily stored at ROKIT Genomics

Temporary Storage Location: ROKIT Genomics, [name]

Storage Conditions: Peripheral blood mononuclear cells (-190°C, liquid nitrogen), serum (-80°C, ultra-low temperature freezer)

Samples are transported to the Korea Institute of Oriental Medicine for storage according to the human-derived material research consent form. Anonymized personal information collected at Kyung Hee University Oriental Medicine Hospital is provided to the Korea

Institute of Oriental Medicine and used solely for human-derived material analysis research, complying with research security regulations. Disposal of human-derived materials is conducted as per the preservation period in the consent form and according to the medical waste disposal manual of the Disease Control and Prevention Agency.

Storage Location: Korea Institute of Oriental Medicine, [name]

Storage Conditions: Peripheral blood mononuclear cells (-190°C, liquid nitrogen), serum (-80°C, ultra-low temperature freezer)

Human-derived materials are preserved for the duration specified in the research consent form and are not used for secondary purposes. No separate consent is obtained for secondary usage, and personal information for secondary use is not attached.

## 1.2 Separation and storage of blood single cells and serum

Separate blood single cells from peripheral venous blood using RBC lysis or density gradient centrifugation. Freeze in cryoprotective medium and store in liquid nitrogen until use. Serum is separated post-clotting (30-60 minutes) and aliquoted into cryovials (0.5ml each, 2-3 cryovials per serum), stored in a freezer box at -80°C until analysis.

### ① Immunological test

Immunological test items, specimen collection and storage, transport method, and sample analysis subject and analysis method etc.

#### 1. Observed items for immunological testing:

- Immune gene expression analysis using single-cell RNA sequencing (scRNA-seq)
- Immunophenotyping analysis using flow cytometry for SARS-CoV-2 specific antibodies
- Quantitative analysis of cytokine levels in serum
- Quantitative analysis of SARS-CoV-2 specific antibodies in serum
- Quantitative analysis of SARS-CoV-2 neutralizing antibody titers in serum
- Immunological testing schedule: Immediately before herbal medicine administration, immediately after administration, 12 weeks post-administration, 24 weeks post-administration (total 4 times)

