## Schedule Summary

| Visit                                                                      | 0       | One  | 2      | 3      | 4       | UV * |
|----------------------------------------------------------------------------|---------|------|--------|--------|---------|------|
| Week (day)                                                                 | -1 (-7) | 1(0) | 4 (28) | 8 (56) | 12 (84) | -    |
| Visit window (day)                                                         | -       | +2   | ±2     | ±2     | ±2      | -    |
| Written Consent                                                            | ●       |      |        |        |         |      |
| Demographic Survey                                                         | ●       |      |        |        |         |      |
| Participation in Other Clinical Trials                                     | ●       |      |        |        |         |      |
| Physical Exam                                                              | ●       |      |        |        |         |      |
| Medical History                                                            | ●       | ●    |        |        |         |      |
| COVID-19 Diagnosis                                                         | ●       |      |        |        |         |      |
| Concomitant Medication/Treatment                                           | ●       |      |        |        |         |      |
| Vital Signs                                                                | ●       | ●    | ●      | ●      | ●       | ●    |
| Electrocardiogram                                                          | ●       |      |        |        | ●       | ●    |
| Laboratory Test                                                            | ●       |      |        |        | ●       | ●    |
| Immune, Metabolite Test (Blood Collection)                                 | ●       |      |        |        | ●       | ●    |
| Pregnancy Status Evaluation **                                             | ●       |      |        |        |         |      |
| Fatigue Symptom Evaluation ***                                             | ●       |      |        |        |         |      |
| FSS (Fatigue Severity Scale)                                               | ●       |      | ●      | ●      | ●       | ●    |

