## **2) Purpose of the Study**

The purpose of this study is to conduct a prospective preliminary clinical trial to evaluate the safety and efficacy of an over-the-counter herbal medicine in individuals who experience fatigue as a symptom of Long COVID after recovering from COVID-19. The trial aims to assess the feasibility of the intervention and research design for future large-scale studies. The primary objective is to explore changes in the Fatigue Severity Scale (FSS) after 12 weeks of taking the herbal medicine (Kyungok-go) in patients with Long COVID-related fatigue. The secondary objective is to evaluate the feasibility of the study design by monitoring recruitment rates and dropout rates during the study period. Additionally, the study aims to explore the

impact of the herbal medicine on COVID-19 immune responses and metabolites associated with fatigue in post-COVID-19 patients.

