### **11.4 Observation and inspection items**

#### **1 1.4.1 Clinical trial progress schedule**

##### **11.4.1.1 Visit 0 ( screening visit)**

Participants who apply to join this clinical trial will receive an explanation of the study and then undergo the following tests. Screening tests can be repeated once within the screening period and must be completed before assigning a participant number. If a retest is conducted, the suitability for participation is determined based on the retest results, and the investigator should document the reasons for the retest, the basis for the decision, and the final results in as much detail as possible.

- ① Before enrolling a clinical trial participant, the principal investigator or the person in charge explains the study process and obtains written consent from the participant.
- ② Screening numbers and random assignment numbers are assigned in the order of written consent completion.
- ③ Investigate and record whether the participant is involved in other clinical trials (within the last 30 days), demographic information, medical history (including diabetes), COVID-19 information (date of onset, recovery date, vaccine details including date, manufacturer, doses, and side effects), past fatigue-related history, and current fatigue symptoms. Even if the participant is receiving diabetes treatment, they can join the study if their test results are within controlled ranges (HbA1c within normal range).
- ④ The physical exam covers general condition, nutritional status, skin/mucosa, eyes (excluding vision impairment), ENT, thyroid, lungs, cardiovascular system, abdomen, renal/urinary system, neurological/psychiatric system, spine/extremities/tumors, peripheral circulation, and lymphatic system.
- ⑤ If possible, confirm and document COVID-19 infection status through the following:
  - SMS notifications from the Disease Control and Prevention Agency regarding confirmed cases.
  - Medical records and diagnostic certificates from the time of COVID-19 diagnosis and treatment.
  - PCR test records from the time of diagnosis.
  - Certificates related to COVID-19 diagnosis or release from quarantine issued by public institutions.
- ⑥ Verify current medications.
- ⑦ Measure vital signs.

- ⑧ Conduct an electrocardiogram (ECG) test.
- ⑨ Collect blood samples for laboratory tests and immune and metabolite analysis (laboratory test results within 28 days of the screening visit can be used):

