## 2 . Experiment method

### 2.1 Single-cell transcriptome analysis using scRNA-seq

Analyze the transcriptome of PBMCs from subjects to assess the distribution and expression of immune cells (B cells, plasma cells, NK cells, CD4 T cells, CD8 T cells, myeloid cells, epithelial cells) and changes in specific immune cells' transcriptome expression (cytokine expression, transcription factors, signal pathways) before and after herbal medicine administration. Sample transport and data analysis for scRNA-seq are conducted by ROKIT Genomics. Create scRNA-seq libraries using the Chromium Single Cell 3' Library & Gel Bead Kit v3 (10xGenomics). Nanoliter-scale droplets isolate thousands of cells, reverse transcribe to cDNA, and assign cell barcoding sequences and UMIs to each cDNA molecule. Analyze sequencing data using the Nextseq 550 or Novaseq 6000 platform (Illumina). Present changes in immune-related gene expression before and after herbal medicine administration using various plots (Barplot-Significant mRNAs, Scatter plot, Volcano plot, Hierarchical clustering heatmap) and summarize candidate mRNAs. Transfer remaining samples to the Korea Institute of Oriental Medicine for storage post-data analysis. Verify selected significant markers via real-time qPCR in individual samples.

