### 2. Items to be observed through metabolite analysis

- The types of metabolites analyzed vary according to LC-MS and GC-MS, as shown in the figure below. In this study, both LC-MS and GC-MS analysis methods are selected to obtain metabolic profiles, including primary and secondary metabolites such as alkaloids and derivatives, benzenoids, homogeneous non-metal compounds, lipids and lipid-like molecules, nucleosides, nucleotides, and analogues, organic acids and derivatives, organic nitrogen compounds, organic oxygen compounds, organohalogen compounds, organoheterocyclic compounds, phenylpropanoids, and polyketides, in the serum. These profiles are used to identify metabolic changes before and after herbal medicine administration.

[figure not shown]

| Sample            | Analysis method                                 | Performing institution                                             | Analysis purpose                                                                                          |
|-------------------|-------------------------------------------------|--------------------------------------------------------------------|-----------------------------------------------------------------------------------------------------------|
| Blood/single cell | scRNA -Seq                                      | ROKIT Genomics                                                     | Verify changes in immune-related transcriptome before and after herbal medicine administration            |
|                   | Real - time qPCR                                | Korea Institute of Oriental Medicine                               | Confirm immune-related transcriptome changes before and after herbal medicine administration              |
|                   | Immunophenotyping using flow cytometry ( FACS ) | Korea Institute of Oriental Medicine                               | Verify changes in immune cell distribution before and after herbal medicine administration                |
| Blood/serum       | Cytokine analysis (CBA )                        | Korea Institute of Oriental Medicine                               | Verify changes in cytokine levels in serum before and after herbal medicine administration                |

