#### **22. Benefits of clinical trial participation**

The costs incurred during the clinical trial (registration, examination, and treatment) will be borne by the investigator. Participants will receive transportation and compensation (a total of 350,000 KRW: 100,000 KRW for 2 visits, 50,000 KRW for 3 visits) when blood is drawn during visits, with 100,000 KRW for visit 4, and 50,000 KRW for other visits (Visits 1, 2, and 3). Non-trial-related medical expenses must be covered by the participants. Transportation and compensation will be provided per visit, post-completion. If participation is discontinued due to dropout or withdrawal, compensation for visits beyond the discontinuation point will not be provided. Payments will be made via bank transfer and may take some time post-visit.

completion. Participants assigned to the placebo group will receive a 12-week supply of Kyungok-go after the trial ends.

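### Immunological sampling is set at four time points although the trial schedules two draws, and immune and metabolite results are described only as before-after change, with no between-arm comparison stated

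*Protocol*

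**What the plan says.** **Sampling times.** Section 11.4.2.11, under the observed items for immunological testing, lists "Immediately before herbal medicine administration, immediately after administration, 12 weeks post-administration, 24 weeks post-administration (total 4 times"). The rest of the Protocol differs:

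- The row "Immune, Metabolite Test (Blood Collection") in the Schedule Summary is marked at Visit 0 (day -7) and Visit 4 (day 84). Its only other mark is for unscheduled visits.
- Section 11.4.1.1 (Visit 0) has the instruction "Collect blood samples for laboratory tests and immune and metabolite analysis". Section 11.4.1.4 (Visit 4) has the matching draw. The descriptions of Visits 1, 2 and 3 have none.
- Section 11.1 ends the study after the 12-week intervention, and Section 11.4.1.4 describes Visit 4 as "marking the end of the clinical trial".
- Section 22 pays "100,000 KRW for 2 visits, 50,000 KRW for 3 visits" and ties the higher rate to blood draws. It also promises the placebo group 12 weeks of Kyungok-go once the trial has ended.

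**Analysis.** The purpose statement in Section 5 includes exploring the "impact of the herbal medicine on COVID-19 immune responses and metabolites associated with fatigue". For scRNA-seq the plan is "Present changes in immune-related gene expression before and after herbal medicine administration using various plots". The specimen table gives the same kind of purpose for every assay, for example "Verify changes in cytokine levels in serum before and after herbal medicine administration". The ANCOVA in Section 14.1 is for efficacy variables. The lists in Sections 14.3 and 15.1 contain no immune or metabolite variable, and the safety analyses in Section 14.4 do not include these markers either.

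**The concern.** The first problem is internal consistency. A site cannot carry out four immunological draws when the visit schedule has two and participation stops at week 12. An analysis plan cannot settle this, because it concerns which samples are taken. Samples after week 12 raise a further difficulty: a placebo participant may by then have started the post-trial Kyungok-go, so the sample might not represent placebo.

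The second problem is interpretation. The objective asks what the drug does, but the only contrast written down is over time. Antibody, cytokine and metabolite levels may drift over 12 weeks for reasons unrelated to treatment, such as time since infection, vaccination or reinfection. A before-after contrast cannot separate such drift from a drug effect, whereas the randomised comparison can. Both arms give blood, so the data for that comparison will exist.

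**Working it through.** **1. Count of draws.** The stated figure is 4. The count from the Schedule Summary and the visit descriptions is 2 (Visit 0 and Visit 4), so the stated figure does not reproduce.

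**2. Both readings of administration.**

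| Stated point | If it means the first dose | If it means the 12-week course |
|---|---|---|
| Before | Visit 0: draw planned | Visit 0: draw planned |
| Immediately after | day of first dose: no draw after dosing | week 12, Visit 4: draw planned |
| 12 weeks post | week 12, Visit 4: draw planned | 12 + 12 = week 24: after trial end |
| 24 weeks post | week 24: after trial end | 12 + 24 = week 36: after trial end |

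On each reading, two of the four points have no planned draw.

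**3. Cross-check on payments (Section 22).** 2 × 100,000 + 3 × 50,000 = 350,000 KRW, which is the stated total. Visit 4 is paid 100,000 and Visits 1 to 3 are paid 3 × 50,000 = 150,000. This leaves 350,000 − 250,000 = 100,000 for the one remaining visit, Visit 0. The payments therefore fit two blood-draw visits.

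**4. Blood volume.** Section 11.4.2.11 takes 25 ml per draw. Two draws are 2 × 25 = 50 ml per participant, and four are 4 × 25 = 100 ml.

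**5. Illustration of the before-after contrast.** The Protocol gives no trend and fixes no paired test, so the trends and the test here are assumptions.

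- Inputs: two-sided alpha 0.05 (Section 14.1). Arm size n = 50 (Section 7, number of subjects), or n = 30 if only Kyung Hee contributes samples. Section 11.4.2.11 places blood sampling within that centre, and Section 7 allots it 30 per arm.
- Assumption: no drug effect, and a trend d common to both arms, in SDs of the change score.
- Formula: the one-arm paired test rejects with probability 1 − F(t*; n−1, d√n) + F(−t*; n−1, d√n). Here F is the noncentral t distribution function and t* is the 97.5% point of t with n−1 degrees of freedom.

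| d (assumed) | d√n, n = 50 | Rejects, n = 50 | d√n, n = 30 | Rejects, n = 30 |
|---|---|---|---|---|
| 0.2 | 1.41 | 0.28 | 1.10 | 0.19 |
| 0.3 | 2.12 | 0.55 | 1.64 | 0.36 |
| 0.5 | 3.54 | 0.93 | 2.74 | 0.75 |

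In the comparison between arms the expected difference is d − d = 0, so its rejection probability is 0.05 for every d and both values of n.

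**The case against.** The strongest reply concerns the analysis. The paragraphs in question are laboratory methods and a table of assay purposes. They fix no statistical test, paired or otherwise, and they exclude no placebo sample. The Protocol also uses herbal medicine for either blinded product: the dosing table in Section 11.2 lists placebo under that heading, and Section 11.4.1.2 dispenses whichever herbal medicine was assigned. Section 14.4.2 describes safety laboratory values before and after administration and then compares the changes between groups, so before-after wording does not rule out a comparison of arms. These markers are exploratory, and their model could sit in a statistical analysis plan that is not shown.

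Much of this stands. A reader might infer that the analysis ignores the placebo arm, or that time trends will be credited to the drug. The documents support neither statement. The lack of a site covariate or of multiplicity control for the marker panels is not a defect here either, since such detail commonly belongs in the analysis plan.

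The reply leaves something unanswered. If herbal medicine covers both products, a before-after comparison is still not a comparison of arms. Section 14.4.2 shows that the Protocol states a between-group contrast when it wants one; for these markers it states none. The scRNA-seq paragraph plans a plot of significant mRNAs and carries the significant markers forward to qPCR, so selection on the before-after contrast is written in.

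On sampling, the other side can say that a single bullet disagrees with several consistent passages, and that no primary, secondary or safety conclusion depends on it. That limits the weight of the contradiction but does not remove it.

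**Conclusion.** The point holds in two parts.

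- **Sampling.** The four-point immunological schedule contradicts the Schedule Summary, Sections 11.1, 11.4.1.1 and 11.4.1.4, and the payments in Section 22. Two of its four points have no draw on either reading. This part rests on no assumption. It applies to immunology only: a reader might extend it to metabolites, but the metabolite text states no schedule of its own and simply shares the Visit 0 and Visit 4 blood.
- **Analysis.** As written, the immune and metabolite results are described only as before-after change, and no between-group method in the Protocol covers them. A trend common to both arms could therefore be read as a drug effect, which is what the objective asks about. The rejection probabilities of 0.19 to 0.93, against 0.05, show how far this could go under assumed trends of 0.2 to 0.5 SD. They do not predict this trial's error rate.

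The consequence is confined to the exploratory immune and metabolite objective.

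**What to change.** 1. Reconcile the testing times in Section 11.4.2.11 with the Schedule Summary, Sections 11.1, 11.4.1.1 and 11.4.1.4, and Section 22. Keeping the two draws at Visit 0 and Visit 4 needs no new samples and only a change of wording. If later samples are really intended, the visits, blood volume, consent and payments must be changed to match. The Protocol must then also say how placebo-arm samples taken after the post-trial Kyungok-go supply are to be interpreted.
2. Add one sentence to Section 11.4.2.11 or Section 14: Visit 4 immune and metabolite values are compared between the randomised arms with adjustment for the Visit 0 value, and within-arm before-after change is given as description only. Marker selection for qPCR should follow the same contrast.

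The cost is Protocol wording. The downside is that fewer markers may look significant.
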